**Methods:**

This is a multicentre, randomised, single-blinded, controlled trial based in early intervention services in National Health Service Mental Health Trusts in six English research sites. Three different methods of providing CRT (intensive, group, and independent) will be compared with treatment as usual. We will recruit 720 service users aged between 16 and 45 over 3 years who have a research diagnosis of non-affective psychosis and will be at least 3 months from the onset of the first episode of psychosis. The primary outcome measure will be the degree to which participants have achieved their stated goals using the Goal Attainment Scale. Secondary outcome measures will include improvements in cognitive function, social function, self-esteem, and clinical symptoms.

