### Outcomes

The ***primary outcome measure*** of the trial is the degree to which participants achieve their personal goals, as measured by the Goal Attainment Scale [46, 47] 15 and 39 weeks after randomisation. The Goal Attainment Scale is a method of scoring the extent to which participant’s individual goals (set at baseline) are achieved during the intervention. In effect, participants each have their own outcome measure but this is scored in a standardised way to allow statistical analysis. The goals are individually identified to suit the participant, and the levels are individually set around their current and expected levels of performance. The Goal Attainment Scale has been adopted in several studies of psychosocial interventions in mental health [48, 49]. It has been shown to be a reliable method of rating behaviours by self-report, which is comparable, but not identical, to informant and researcher reports, and has wide use in studies of cognitive rehabilitation and in clinical practice [50–52].

The ***secondary outcome measures***, some of which are used in the cost-effectiveness analysis, are: (a) social and occupational functioning, as measured by the Time Use Survey [53] and the EuroQOL five dimensions questionnaire [54]; (b) use of services, as measured by the Client Service Receipt Inventory [55]; (c) self-esteem, as measured by the Rosenberg Self-Esteem Scale [56]; and (d) cognition, as measured by the Cambridge Neuropsychological Test Automated Battery (which includes the following tests: Reaction Time, One-Touch Stockings of Cambridge, Paired-Associates Learning, Attention Switching Task, Rapid Visual Information Processing, Spatial Working Memory and Emotion Recognition Task) and supplemented by the Computerized Wisconsin Card Sorting Task [57], Rey Auditory Verbal Learning Test [58], Rey Osterrieth Complex Figure [59] and Digit Span forwards and back test [60]. We also collect some background data to investigate treatment mechanisms, including the Wechsler Abbreviated Scale of Intelligence [61] and metacognition measures. A description of these outcomes is presented in Additional file 2: Table S1.

Data are collected by trained research assistants, whose reliability is assessed regularly. Consistency between sites is achieved by regular review by members of the management and research teams as well as data quality checks at the site and by audit through the trial statistician.

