### Measurement

#### Power

We have the capacity to recruit 900 patients (from 1500 patients attending 10 services for 3 years) and have allowed for a 20% drop-out pre-randomisation. Using a design with parallel arms of equal size, with 180 patients per arm, provides approximately 80% power for a simple group effect size difference of 0.3. This increases to 91% for outcomes that correlate 0.5 with baseline (both calculated using sampsi in Stata).

Freidlin *et al.* [62] suggest no great advantage in accounting for multiple testing in a multi-arm trial, and also that the advantages of a larger treatment-as-usual arm are more slight than commonly assumed. Interaction among patients in group delivery is very slight so no allowance for clustering was thought necessary.

The power calculation is based on arms of equal size; the difference in power as a result of the unequal allocation is likely to be small as the use of modestly unequal randomisation ratios only very slightly reduces the power of a study [63].

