#### Analysis

***The primary outcome measure*** will be group differences in Goal Attainment Scale T-score [47] at 15 weeks post-randomisation, tested using an analysis of covariance (ANCOVA) model co-varying for Goal Attainment Scale T-score at baseline and adjusting for site as a fixed effect. Pairwise comparisons will be conducted between each of the CRT arms and treatment as usual, with significance and confidence intervals calculated using nominal values of *p*. Data will be analysed under intention-to-treat assumptions. Treatment effects for secondary outcomes will be analysed in a similar way. For the primary outcome, given the probable differences in treatment uptake (adherence), local average or complier average treatment effects compared with treatment as usual will also be estimated. Using assigned arm as an instrumental variable, all arms will be examined together to estimate the effect of hours of active CRT. On an assumption of a common per-hour effect across arms, some residual information will be available to estimate residual direct effects of treatment mode.

The ***cost-effectiveness*** analysis will be conducted from the perspectives of health and social care and society (including informal care, lost employment). Service use, collected using the Client Service Receipt Inventory, will be combined with appropriate unit cost information [64] and added to the intervention costs. Costs will be compared between groups using bootstrapped regression models to address the probable skewed distribution. Cost-effectiveness will be assessed by combining costs and outcome measures (primary outcome measure and quality-adjusted life years) in the form of incremental cost-effectiveness ratios.

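### The primary ANCOVA's only covariate besides site is a baseline goal score likely to predict little; one or two baseline measures already collected would be a cheap addition

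*Protocol article*

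**What the plan says.** The Power section of the protocol article states that a design of equal arms, "with 180 patients per arm, provides approximately 80% power for a simple group effect size difference of 0.3". It continues: "This increases to 91% for outcomes that correlate 0.5 with baseline". It gives no source for the 0.5 and does not name the outcomes meant.

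The Analysis section fixes the primary model as an ANCOVA on the 15-week Goal Attainment Scale T-score, "co-varying for Goal Attainment Scale T-score at baseline" and with site as a fixed effect. No other covariate is named. Secondary outcomes are to be handled in a similar way.

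The Outcomes section explains how the scale is built. Goals are chosen at baseline, the score reflects how far they are reached during the intervention, and "the levels are individually set around their current and expected levels of performance". The same section lists the Time Use Survey and a wide cognitive battery as secondary measures, and the Trial design section has outcomes measured at baseline as well as at 15 and 39 weeks.

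**The concern.** A baseline value of the outcome usually earns its place in an ANCOVA because people who start high tend to finish high. A scale centred on each person's own starting point removes much of that between-person difference. The baseline T-score may then have little spread and carry little information about later attainment, yet it is the only prognostic covariate in the primary model besides site.

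Two things follow. A reader who sees one primary outcome, an ANCOVA on its own baseline, and a power of 91% could take 91% as the power of the primary test. And the model leaves unused baseline measures that the protocol itself treats as prognostic. The Background section says that poor cognition is a key predictor of poor functional outcome, and that people with the most cognitive difficulty gain least from rehabilitation.

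**Working it through.** **Inputs from the protocol article.** 180 per arm and effect size 0.3 (Power); 720 participants in total (Abstract, Methods); allocation 4:4:3:4 for group, independent, intensive and treatment as usual (Allocation and blinding).

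**Assumptions.** Two-sided alpha of 0.05, which the Power section does not state but which reproduces both of its figures. Outcome SD of 1 before adjustment. Every block a full block of 15. No loss after randomisation. The correlation r between covariates and outcome is not given anywhere, so it is shown as a range.

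**Formula.** The residual SD after adjustment is √(1 − r²). Power is approximately Φ(0.3 / [√(1 − r²) × √(1/n₁ + 1/n₂)] − 1.96).

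**The plan's own figures, 180 v 180.** √(2/180) = 0.1054.
- r = 0: 0.3/0.1054 = 2.846; 2.846 − 1.96 = 0.886; power 81.2%, against about 80% stated.
- r = 0.5: residual SD 0.866; 2.846/0.866 = 3.286; 3.286 − 1.96 = 1.326; power 90.8%, against 91% stated.

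Both reproduce. Using the noncentral t instead gives 81.0% and 90.6%.

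**Planned allocation.** 720/15 = 48 blocks, so intensive CRT has 48 × 3 = 144 and treatment as usual 48 × 4 = 192. √(1/144 + 1/192) = 0.1102, and 0.3/0.1102 = 2.721.

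| r | 180 v 180 | Intensive v usual, 144 v 192 | Gain over r = 0, intensive contrast |
|---|---|---|---|
| 0 | 81.2% | 77.7% | – |
| 0.1 | 81.6% | 78.1% | 0.4 points |
| 0.2 | 82.8% | 79.3% | 1.6 points |
| 0.3 | 84.7% | 81.4% | 3.7 points |
| 0.5 | 90.8% | 88.2% | 10.5 points |

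The group and independent arms against treatment as usual (192 v 192) have 83.6% at r = 0 and 86.9% at r = 0.3.

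**Reading the table.** The step from about 81% to 91% comes wholly from r = 0.5, which removes r² = 25% of the outcome variance. At r = 0.2 only 4% is removed. Reaching 91% would take 243 per arm at r = 0, against 182 at r = 0.5.

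The same table gives the value of adding covariates, if r is read as the multiple correlation of the whole covariate set and the baseline T-score contributes nothing. A joint value of 0.3 moves the intensive contrast from 77.7% to 81.4%.

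**The case against.** The strongest reply is that the Power section makes no false claim. The 91% is conditional and speaks of outcomes in the plural. The headline of about 80% needs no correlation, so the sample size does not rest on 0.5. That stands in full: on the power wording, all that can be asked is a clarification.

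A second reply is that the documents do not show the baseline score to be uninformative. A reader might infer from the way the scale is built that everyone starts at the same score, so that r must be near zero. The text does not support that. Levels are set around current and expected performance, no rule assigns a common starting level, and no scoring formula or baseline distribution is given. Some spread and some correlation remain possible. This also stands, which is why r is shown as a range.

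A third reply is that extra covariates are a matter of preference. A model with baseline and site is valid, and a weak covariate does it no harm. If anchoring removes baseline status from the score, cognition and time use might not predict attainment either. This stands in part. The gain is uncertain and could be close to nil. But the Background's statement that those with the most cognitive difficulty gain least concerns improvement rather than level, so it bears on a score of goals achieved. It comes from rehabilitation generally, though, and not from this scale.

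The statistical analysis plan is not shown and may name further covariates. The article, however, does specify the primary model, so this is a comment on a stated choice and not on an omission.

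**Conclusion.** The primary analysis is valid, and the stated powers are arithmetically right. It would be wrong to conclude that 91% is an error or that the comparison at 180 per arm is underpowered: the conditional wording and the 81.2% at r = 0 rule out both.

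What holds is narrower. The one prognostic covariate besides site is likely, though not shown, to be weak. For r between 0 and 0.3, primary-outcome power is 81% to 85% at 180 per arm and 78% to 81% for intensive CRT against treatment as usual. These figures assume two-sided 0.05, an effect size of 0.3, full blocks of 15, 720 randomised and no loss. Baseline measures already collected offer a small gain in precision at almost no cost. That gain matters most for the intensive contrast, which falls slightly below 80% if the covariates carry no information.

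**What to change.** 1. Keep the baseline T-score and site in the primary ANCOVA. Add one or two pre-specified baseline predictors: a cognitive composite, defined in advance from the listed tests, and Time Use Survey hours. Fix the choice, and a simple rule for missing baseline values, before unblinding; the Allocation and blinding section already requires analysis scripts to be final by then.
2. In the Power section, say that 91% refers to outcomes such as cognition, with a source for the 0.5, and that about 80% is the figure for goal attainment. Show primary-outcome power for r from 0 to 0.3 at the planned allocation.

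The first change costs a few degrees of freedom and some wording, with no new data collection. The second is wording only.

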Therapy will be delivered at each site by an experienced assistant psychologist trained in CRT at the trial centre and supervised centrally on a weekly basis. Each therapist will provide all three types of CRT over the therapy period.***Intensive CRT***. Participants will receive 10.5 weeks of twice weekly therapy, up to 42 h in total, with sessions lasting between 60 and 180 min, split into three parts: (1) 20–60 min of CRT with a therapist; (2) 20–60 min of *in-vivo* transfer work (i.e. putting CRT strategies into real life) with a therapist; (3) 20–60 min of independent CRT, set up by the therapist on-site, or off-site in the service user’s own time.***Group CRT***. Participants randomised in this arm will be offered 14 weeks of thrice weekly group therapy (up to 42 h of CRT). Group sessions will last up to 90 min, with attendance for at least 20 min considered as a completed session. Groups have closed membership, with four participants per group and one therapist. The sessions will begin and end with group activities, relating to goal setting and metacognition. During the rest of the session, service users will work independently on CIRCuiTS tasks, with the therapist offering help and support on an as-needed basis.***Independent CRT.*** Participants will receive one individual session with the therapist for orientation followed by up to 41 sessions when they will work independently (up to 42 h of CRT in total). To support the independent sessions, the therapist will offer telephone contact or attendance at drop-in sessions on an as-needed basis to address any questions or problems (but not exceeding 1 h contact time per fortnight). A session will be considered ‘valid’ if it lasts a minimum of 20 min.***Treatment as usual.*** This will be the standard input offered by the treating team without restrictions. Standard care involves clinical contact with the team on a daily, weekly or monthly basis depending on recovery. It also involves opportunities to be involved in educational or employment programmes, other psychological therapies, e.g. cognitive behaviour therapy for psychosis and medical treatments, including drug therapies. Participants randomised to the treatment-as-usual group will not receive CRT therapy.

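### The plan dismisses clustering in the group CRT arm without an ICC or a source; if outcomes within therapy groups are correlated at all, standard errors for group-arm contrasts are too small, modestly so with groups of four

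*Protocol article*

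**What the plan says.** The Power section sizes the trial as individually randomised: "Using a design with parallel arms of equal size, with 180 patients per arm". The result claimed for this design is that it "provides approximately 80% power for a simple group effect size difference of 0.3". It adds: "This increases to 91% for outcomes that correlate 0.5 with baseline". Clustering is considered and set aside in one sentence: "Interaction among patients in group delivery is very slight so no allowance for clustering was thought necessary". No ICC, range or source is given.

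The Analysis section fixes the primary model as an ANCOVA of the Goal Attainment Scale T-score at 15 weeks, with baseline score as covariate and site as a fixed effect. Each CRT arm is compared with treatment as usual, "with significance and confidence intervals calculated using nominal values of" *p*. Secondary outcomes follow the same approach. No therapy-group term or group-robust variance is named.

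The Interventions section describes the group arm: "Groups have closed membership, with four participants per group and one therapist". Sessions are offered three times a week for 14 weeks. "The sessions will begin and end with group activities, relating to goal setting and metacognition". Between those activities, participants work on their own on the computerised tasks, with therapist help when needed.

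**The concern.** The group arm is partially nested: its participants are treated in fixed groups of four, while participants in the other arms are not treated in groups. An ANCOVA that treats all participants as independent understates the variance of the group-arm mean if outcomes within a therapy group are positively correlated.

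The reason given for ignoring this covers only interaction between patients. Members of a closed group also share the same sessions and the same calendar period. The site fixed effect removes differences between sites but not between successive groups at one site. The shared activities concern goal setting, which is close to what the primary outcome measures.

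The trial exists to choose between delivery modes, so it matters if one mode's result looks more precise than it is. The nominal p-values leave no margin to absorb the excess error. The economic analysis is exposed too. The Interim analysis section derives direct therapy costs partly from the number of attendees in group therapy, so costs of members of the same group are linked. A bootstrap that resamples individuals would ignore that link.

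**Working it through.** **Inputs from the protocol article.** 180 per arm and d = 0.3 (Power); baseline correlation r = 0.5 for the adjusted figure (Power); group size m = 4 (Interventions).

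**Assumptions.** Two-sided alpha of 0.05, which the article does not state but which reproduces both of its powers. Within-group ICC of 0.01 to 0.20, since the article gives none. The ICC is applied to the residual variance in the adjusted case.

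**Step 1: reproduce the stated power.** Power = Φ(d/SE − 1.96), with SE = σ√(1/180 + 1/180).

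- Unadjusted, σ = 1: SE = 0.1054; 0.3/0.1054 = 2.846; Φ(0.886) = 81.2% (stated: about 80%).
- Adjusted, σ = √(1 − 0.5²) = 0.866: SE = 0.0913; 0.3/0.0913 = 3.286; Φ(1.326) = 90.8% (stated: 91%).

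Both stated powers therefore reproduce as unclustered figures.

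**Step 2: add clustering in the group arm only.** Design effect DE = 1 + (4 − 1) × ICC. True SE = σ√(DE/180 + 1/180), so true SE / naive SE = √((DE + 1)/2). Type I error of the naive test = 2 × [1 − Φ(1.96 / ratio)]. Power with the correct SE = Φ(0.3/true SE − 1.96).

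Example at ICC 0.05: DE = 1 + 3 × 0.05 = 1.15; effective n = 180/1.15 = 157; ratio = √(2.15/2) = 1.037; type I error = 2 × [1 − Φ(1.890)] = 5.9%; true SE = √(2.15/180) = 0.1093; power = Φ(2.745 − 1.96) = 78.4%.

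| Assumed ICC | DE | Effective n, group arm | True/naive SE | Type I error | Power, unadjusted | Power, r = 0.5 |
|---|---|---|---|---|---|---|
| 0 | 1.00 | 180 | 1.000 | 5.0% | 81.2% | 90.8% |
| 0.01 | 1.03 | 175 | 1.007 | 5.2% | 80.6% | 90.4% |
| 0.05 | 1.15 | 157 | 1.037 | 5.9% | 78.4% | 88.7% |
| 0.10 | 1.30 | 138 | 1.072 | 6.8% | 75.6% | 86.5% |
| 0.20 | 1.60 | 112.5 | 1.140 | 8.6% | 70.4% | 82.2% |

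**Step 3: check against the stated model.** The four-arm ANCOVA with baseline and site fixed effects was simulated with 48 full blocks of 15 (720 participants) and 6,000 runs per ICC. Type I error for group CRT versus treatment as usual was 4.9% at ICC 0, 6.3% at 0.05, 7.4% at 0.10 and 8.5% at 0.20. The Monte Carlo standard error is about 0.3 to 0.4 percentage points. The formula values are close to these and do not exaggerate the problem at ICC 0.05 and 0.10.

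**The case against.** The sponsor can defend its judgement on several grounds, and much of the defence stands.

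- *Most of the session is individual.* Shared activities only open and close a session of up to 90 minutes. A reader might infer that goals are set jointly at every session, so that the article flatly contradicts itself. It does not say that: it describes group activities relating to goal setting and metacognition. The stated reason is poorly supported rather than refuted.
- *Outcome goals are individual.* The Outcomes section has goals set at baseline to suit each participant, and participants are assessed before allocation. The goals therefore precede the group. Attainment of them can still be correlated among people who went through the same sessions, but no figure in the article shows that it is.
- *The therapist is not specific to a group.* Each therapist delivers all three CRT modes, and therapy is delivered site by site, so the site effect absorbs some therapist variation. It does not absorb differences between successive groups.
- *The effect may be negligible.* At ICC 0.01, which would suit the sponsor's view of slight interaction, the standard error is off by 0.7%. With r = 0.5, power stays above 80% even at ICC 0.20.
- *The scope is limited.* Of the three contrasts with treatment as usual that the Analysis section names, only one involves the group arm.
- *The SAP is not shown and may add a group term.* That is possible. But the article does more than stay silent: it decides that no allowance is needed and names a model without one.

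**Conclusion.** The point holds in conditional form. If the within-group ICC is above zero, the planned analysis understates the standard error for group CRT versus treatment as usual, and for any other contrast involving the group arm. The direction follows from the design. The size depends on an ICC that the article does not give.

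Over an assumed range of 0.01 to 0.10 the standard error is too small by a factor of 1.007 to 1.072. Type I error is 5.2% to 6.8% in place of 5%. Correctly computed power is 80.6% down to 75.6% unadjusted, or 90.4% down to 86.5% with r = 0.5.

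A reader might infer that the group arm's standard errors are certainly too small, or that the arm is underpowered. The document supports neither: the first needs a positive ICC, and the second depends on both the ICC and the baseline correlation. This is a modest, cheaply corrected weakness that should be put right. It does not undermine the trial.

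**What to change.** 1. Record each group-arm participant's therapy group as a variable in the trial data.
2. For the primary and secondary outcomes, fit a partially nested model: a random therapy-group effect in the group arm only, with all other participants as singletons. Standard errors robust to therapy group are an acceptable alternative.
3. In the cost-effectiveness bootstrap, resample whole therapy groups in the group arm. Apply this to the interim analysis too: its first 195 participants would contain only about 13 therapy groups if every block is full (195/15).
4. Replace the sentence that makes no allowance with the group arm's power over a range of ICCs, for example 0.01 to 0.10, using the figures under the working.

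The cost is small. Therapy-group membership follows from the randomisation block, no more participants are required, and the wording change is short. The price is slightly wider intervals for group-arm contrasts: about 4% wider at ICC 0.05, and under 1% at ICC 0.01.
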